#### Health economic measures

Health economics outcome measures are included in the trial to assess for resource utilisation (Client Service Receipt Inventory (CSRI) [61]), productivity loss (iMTA Productivity Cost Questionnaire (iPCQ) [62]), quality of life (EuroQol 5 Dimensions 5 Levels health survey (EQ-5D-5L) [63] and Recovering Quality of Life Questionnaire (Re-QoL) [64]), and health problems (Short Form Health and Labour Questionnaire (SF-HLQ) [65]). These measures were chosen with the assistance of a health economist, and some of the measures have been shortened due to overlapping questions. Health economic measures will be administered at baseline, 8 weeks post-random allocation, and at 6 months post-intervention follow-up for secondary analyses. Between-group differences will be measured at 8 weeks post-random allocation for quality of life, and within-group analyses including everyone who received the SHAPE intervention will be conducted at 6 months post-intervention completion to compare productivity loss, resource utilisation, and health problems from pre- to post-intervention. Results will be published separately from the primary and secondary psychological outcomes.

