**Methods:**

The trial will include two parallel conditions (intervention and waitlist) using a 1:1 allocation ratio. Assessors of treatment outcome will be blinded to trial condition. Ninety-two participants who meet criteria for PTSD or MDD will be randomly allocated to the intervention or waitlist condition, minimising for key clinical characteristics. Participants allocated to waitlist will be offered the SHAPE intervention afterwards. The intervention will be tailored CT coaching for PTSD and MDD called SHAPE. The primary assessment point is 8 weeks post-random allocation. Further assessment points are 4 weeks post-random allocation and 6 months after receiving the intervention to measure the long-term effects of SHAPE. The primary outcome is SCID-5 diagnosed PTSD and MDD at 8 weeks post-random allocation. The PTSD Checklist for DSM-5 (PCL-5) and the Patient Health Questionnaire (PHQ-9) will be used as secondary measures of PTSD and MDD to assess for symptom severity. Other secondary measures will assess for posttraumatic cognitions, responses to intrusive memories, resilience, wellbeing, and symptom severity for generalised anxiety disorder and insomnia. Health economic analyses will compare the two conditions on quality of life at 8 weeks post-random allocation and compare productivity loss, resource use, and health problems at pre- and post-intervention for everyone who received SHAPE. Patient and provider experience of the SHAPE intervention will be assessed by semi-structured interviews at post-intervention.

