#### Explanation for choice of comparator {9b}

The comparator will be an 8-week waitlist control condition. Since some individuals with PTSD experience recovery over time, a waitlist comparison allows us to distinguish intervention-specific effects from those associated with the passage of time.

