#### Health economic measures

This study will also collect health economics outcomes to assess resource utilisation, productivity loss, quality of life, and health status. Health economic measures will be administered at baseline, 8 weeks post-random allocation, and 6 months post-intervention completion for secondary analyses.

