### Methods for additional analyses (e.g. subgroup analyses) {27d}

#### Health economic evaluation

A health economics evaluation will compare the costs involved in administering SHAPE and the costs saved in terms of patient quality of life, working hours, and use of healthcare services. Health economic measures including the iMTA Productivity Cost Questionnaire short (iPCQ) [62], Short Form Health and Labour Questionnaire (SF-HLQ) [65], Client Service Receipt Inventory (CSRI) (*edited*) [61], Quality of Life (EQ-5D-5L) [63], and Recovering Quality of Life (Re-QoL) [64] will be collected at baseline (0 weeks), 8 weeks post-random allocation, and at 6 months post-intervention follow-up. Results will be expressed in costs per group.

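### Productivity, service use and health problems have only a before-after comparison, and the plan does not say whether its savings statement rests on it

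*Protocol article*

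**What the plan says.** The Health economic measures section under Measures lists five instruments: CSRI for resource use, iPCQ for productivity loss, SF-HLQ for health problems, and EQ-5D-5L and Re-QoL for quality of life. On timing it states: "Health economic measures will be administered at baseline, 8 weeks post-random allocation, and at 6 months post-intervention follow-up for secondary analyses". The Outcomes section {16} gives the same schedule, and neither section limits any instrument to one arm.

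The analysis is split between quality of life, compared between arms at week 8, and the other three measures: "Between-group differences will be measured at 8 weeks post-random allocation for quality of life, and within-group analyses including everyone who received the SHAPE intervention". The within-group analyses "will be conducted at 6 months post-intervention completion to compare productivity loss, resource utilisation, and health problems from pre- to post-intervention". The abstract says the same: the trial will "compare productivity loss, resource use, and health problems at pre- and post-intervention for everyone who received SHAPE". Objectives {10} again describes these items as measured before SHAPE and 6 months after it.

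The Health economic evaluation section {27d} then sets the cost of giving SHAPE against "costs saved in terms of patient quality of life, working hours, and use of healthcare services" and says that results will be given as costs per group. It names neither the contrast nor the groups.

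**The concern.** To say that costs were saved is to say that they would have been higher without SHAPE. A before-after change in treated people cannot show that. Participants enter with current PTSD or MDD, and some would recover, use fewer services and lose less work time untreated. The protocol gives this as its reason for a control: "a waitlist comparison allows us to distinguish intervention-specific effects from those associated with the passage of time". The abstract's discussion makes the same argument.

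For working hours and service use, the only comparison described does not use that control, although week-8 data on the same instruments are collected. If the savings statement is built on it, the economic paper could report natural improvement as a return on the intervention. The primary efficacy result is not affected.

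**Working it through.** **1. Which comparison does each measure get?**
- Quality of life (EQ-5D-5L, Re-QoL): randomised, week 8.
- Productivity loss, resource use, health problems: before versus after, in everyone who received SHAPE, including waitlist participants treated later. The abstract, Objectives {10} and Health economic measures agree.
- Outcomes {16} makes comparison between conditions the default unless something else is specified. Health economic measures does specify something else for these three, so the default does not rescue them.

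**2. Are week-8 data available in both arms?** One schedule sentence covers all five instruments, and the between-arm quality-of-life analysis requires that schedule to apply to both arms at week 8. The text gives no reason to think the other three differ; Fig. 2 should be checked to confirm it.

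**3. The protocol's rates, checked through its sample size.** Inputs from Sample size {19}: recovery 50% versus 16%, 90% power, alpha 0.05 (taken as two-sided), 15% attrition. With pooled variance and mean proportion 0.33:

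n = [1.960 × √(2 × 0.33 × 0.67) + 1.282 × √(0.50 × 0.50 + 0.16 × 0.84)]² / 0.34² = (1.303 + 0.795)² / 0.1156 ≈ 38.1, so 39 per arm.

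Attrition: 39 / 0.85 = 45.9, so 46 per arm and 92 in total. The stated figures reproduce. There is no power figure for the economic evaluation.

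**4. How much recovery would occur untreated?** The same section gives natural recovery of 12 to 20% over 2 to 3 months. Share = untreated rate / SHAPE rate; overstatement = SHAPE rate / (SHAPE rate − untreated rate).
- 12%: share 0.12 / 0.50 = 24%; difference 38 points; factor 0.50 / 0.38 = 1.32.
- 16%: share 0.16 / 0.50 = 32%; difference 34 points; factor 0.50 / 0.34 = 1.47.
- 20%: share 0.20 / 0.50 = 40%; difference 30 points; factor 0.50 / 0.30 = 1.67.

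These are shares of diagnostic recovery. They carry over to costs only if costs move in proportion to recovery, which the documents do not address.

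**5. What precision would a week-8 comparison have?** The half-width of a 95% interval for a difference in means, in SD units (normal approximation, unadjusted), is 1.96 × √(2/n). With 39 per arm this is 0.44 SD; with 46 per arm, 0.41 SD.

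**The case against.** The link between the two economics sections is an inference. Health economic evaluation does not mention a before-after analysis, and costs per group can be read as costs per trial arm. Quality of life, which that section counts among the savings, already has a randomised comparison. This stands: a reader might infer that the plan has committed itself to deriving savings from uncontrolled change, and the text does not go that far. It leaves the contrast undefined, while the only contrast stated elsewhere for working hours and service use is uncontrolled.

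The Discussion already concedes that, without a comparison between conditions at 6 months, changes at that point cannot be shown to be specific to the intervention. A control at 6 months is impossible because waitlist participants are offered SHAPE after week 8. Both points are right, but the concession is not carried into the economics sections and does not explain why week 8 is unused for these measures.

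A week-8 comparison also has weaknesses. Eight weeks is short and the intervals are wide. Waitlist participants are asked not to take up psychological support or change medication, and Concomitant care {15d} sets similar limits for everyone, so week-8 service use is not usual service use. These are limits to report. The restrictions apply in both arms over those weeks.

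Two stronger readings should be resisted. A reader might take the 24 to 40% as the fraction of reported savings that is spurious; with no cost data, the documents do not support that. Recovery over 2 to 3 months also does not describe change to 6 months after treatment, and if waitlist participants are counted from their post-wait scores, as in the main follow-up analyses, their starting point is later still. A reader might also tie the problem to the Discussion's remark that SHAPE may be cost-effective. That remark is conditional on superiority and argued from the shorter treatment time, not from this analysis.

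**Conclusion.** The point holds in a limited form. The protocol fixes an uncontrolled comparison for productivity loss, resource use and health problems, reserves the randomised week-8 comparison for quality of life, and does not say which contrast supports its savings statement. If the before-after analysis is used, the effect of time is credited to SHAPE. The expected direction is to flatter SHAPE, provided that costs fall as people recover. The amount is unknown: the 24 to 40% (32% at the planning rate of 16%) shows only that natural recovery is not negligible on the protocol's own assumptions. This is a secondary matter, but an inexpensive one to correct, and because the article states the choice itself it is not a detail left to the analysis plan.

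**What to change.** - Add a week-8 comparison of iPCQ, CSRI and SF-HLQ between arms as randomised, adjusted for baseline and the three minimisation factors, with bootstrap intervals for skewed costs. Report it as an estimate with its interval.
- Reconcile Health economic measures with Health economic evaluation: define group, name the contrast, and let any savings statement on working hours or service use rest on the week-8 comparison.
- Keep the 6-month before-after analysis, label it descriptive, and repeat there the limitation given in the Discussion.
- State the limits: an 8-week horizon, intervals of roughly ±0.41 to 0.44 SD before adjustment, and service use partly restricted by trial rules in both arms.
- If week-8 cost data have already been examined, date the change and say so.

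The cost is a few lines of text and one extra set of models, with no further participants, visits or questionnaires. The economic results are to be published separately, so the main trial report is not affected.

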### Eligibility criteria for participants {14a}

Table 1 outlines the inclusion and exclusion criteria for the study. Eligibility criteria were chosen to allow for a wide range of HSCWs experiencing symptoms of PTSD or MDD to participate in the trial.

**Table 1 Tab1:** Randomised controlled trial for Supporting Healthcare and Paramedic Employees (SHAPE): Inclusion and exclusion criteria

Inclusion criteria
1. Aged 18 years and older
2. Patient-facing health or social care worker—professions can include nurse, doctor, paramedic, midwife, care worker, ambulance service team member, allied health professional, mental health professional, healthcare support worker, medical associate, pharmacist, care assistant, and nursing or medical student working in a healthcare setting
3. PTSD or MDD is the primary disorder requiring treatment (i.e. the main clinical condition currently warranting treatment, as determined during the clinical assessment)
4. Diagnosed with PTSD or MDD on the Structured Clinical Interview for DSM-5 (SCID-5) PTSD or MDD module
5. Willing and able to provide informed consent
6. Willing to be randomised
7. If taking psychotropic medication, the dose must be stable for at least 1 month before randomisation and remain stable throughout the trial
8. If currently receiving psychological therapy, the treatment must have ended before randomisation
9. Any current re-experiencing symptoms are linked to no more than 2 discrete traumatic events that have occurred at or outside of work, or several traumatic episodes during a longer period of high threat (e.g. domestic abuse, childhood abuse, COVID-19, prolonged work trauma)
Exclusion criteria
1. Imminent, persistent, clinically significant risk which needs immediate attention, or which would interfere with the capacity to engage in the trial
2. Request for face-to-face treatment for PTSD or MDD
3. Preference for a counselling approach, or trauma-focused therapy within NHS Talking Therapies
4. Previously received the SHAPE intervention before joining the trial

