#### Waitlist condition

Participants randomly allocated to the waitlist condition will not receive any therapeutic support from their assigned coach or the research team during the 8-week waiting period. Participants are asked not to take up psychological support during the waiting period (i.e. CBT, counselling) or change their current psychotropic medication if they are already taking it to allow for a clean comparison between conditions. If a participant wishes to access the SHAPE intervention, they will be able to receive the intervention after they complete their post-wait measures and have their second telephone assessment at 8 weeks post-random allocation. If a participant no longer wishes to receive the intervention, they can opt out and will be provided with relevant information on alternative services if requested.

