### Concomitant care permitted or prohibited during the trial {15d}

Prior to beginning treatment, all participants will be instructed to refrain from receiving other psychological treatment during the trial. Participants will be advised that trial eligibility requires that they do not start new psychotropic medications during the trial and remain on a stable dose of their current psychotropic medication if they are taking medication. All urgent and unexpected concomitant psychological interventions, treatments, and changes in medication that do occur during the trial will be documented in the research trial records as soon as the research team are made aware of this.

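### Part of any fall in psychological-therapy use after SHAPE may come from the trial's own restrictions, yet the health economic plan would let it count as a cost saved

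*Protocol article*

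**What the plan says.** Under Health economic measures, the article fixes the comparison for resource use, productivity and health problems: "within-group analyses including everyone who received the SHAPE intervention will be conducted at 6 months post-intervention completion", in order "to compare productivity loss, resource utilisation, and health problems from pre- to post-intervention". Resource use is measured with the Client Service Receipt Inventory (CSRI). The only randomised health economic comparison concerns a different outcome: "Between-group differences will be measured at 8 weeks post-random allocation for quality of life". The data are collected more widely than they are compared: "Health economic measures will be administered at baseline, 8 weeks post-random allocation, and at 6 months post-intervention follow-up for secondary analyses".

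The section Health economic evaluation sets the cost of delivering SHAPE against "the costs saved in terms of patient quality of life, working hours, and use of healthcare services".

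Three rules elsewhere restrict part of what the CSRI may record. Table 1 (inclusion criterion 8) says: "If currently receiving psychological therapy, the treatment must have ended before randomisation". Section {15d} says: "all participants will be instructed to refrain from receiving other psychological treatment during the trial". It also asks participants to start no new psychotropic drug and to keep any current dose stable. For the delayed arm, the Waitlist condition section says: "Participants are asked not to take up psychological support during the waiting period". Section {15d} adds that urgent and unexpected treatments and medication changes will be documented.

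**The concern.** A pre-post difference in service use is read as the effect of the intervention only if nothing else systematically changes between the two periods. Here the trial changes something itself. Before entry a person may be in therapy; to enter, that therapy must stop; after entry, the person is told not to take up more. A SHAPE programme with no effect on help-seeking could still show lower therapy use afterwards, and the evaluation as written would credit that to SHAPE.

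This differs from the usual weakness of an uncontrolled comparison. The Discussion concedes that changes at 6 months cannot be shown to be specific to the intervention, but it does not mention that the protocol restricts one of the services being costed. At stake is a secondary result, to be published separately, that bears on the Discussion's suggestion that SHAPE may be cost-effective and scalable.

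**Working it through.** No figure for resource use is stated in the article, so there is nothing to reproduce. The check is a reading of the rules against the comparison, followed by an illustration of size.

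**Step 1: which period each rule covers.**

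- *Before period, immediate arm.* The baseline questionnaires come just before randomisation. If the CSRI looks back over a period, that period can contain therapy that inclusion criterion 8 then required to end.
- *After period.* Section {15d} applies during the trial. Section {27a and 27b} places the conclusion of the trial period after the 6-month follow-up, and section {34} has participants returning to usual treatment after completing the trial. On this wording the instruction covers the follow-up window.
- *Before period, delayed arm.* The Follow-up analyses section takes the post-wait assessment as the pre-intervention point for these participants. If the health economic analysis does the same, which is not stated, their reference period follows 8 weeks in which they were asked not to take up psychological support. The pooled group would then mix unrestricted and restricted reference periods.

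**Step 2: direction by type of service.**

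- Psychological therapy: possible before, discouraged after. Any artefact runs toward apparent savings.
- Psychotropic medication: no new drug and a stable dose. The rule discourages rises and falls alike, so the change says little and is not pushed downward.
- All other healthcare: not restricted, so no artefact from these rules.

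**Step 3: size with no SHAPE effect.** All inputs are assumptions, none from the documents:

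- q = share of participants with therapy in an unrestricted before window
- s = sessions per such participant, set to 6
- c = share of that use removed by the restriction
- w = share of the sample whose before window is already restricted

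Mean use before = (1 − w)·q·s + w·q·s·(1 − c). Mean use after = q·s·(1 − c). The difference is (1 − w)·q·s·c.

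| q | w = 0, c = 1 | w = 0, c = 0.5 | w = 0.5, c = 1 | w = 0.5, c = 0.5 |
|---|---|---|---|---|
| 0% | 0 | 0 | 0 | 0 |
| 10% | 0.6 | 0.3 | 0.3 | 0.15 |
| 20% | 1.2 | 0.6 | 0.6 | 0.3 |
| 40% | 2.4 | 1.2 | 1.2 | 0.6 |

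Entries are sessions per participant. For example, q = 20%, w = 0, c = 1 gives 1 × 0.20 × 6 × 1 = 1.2. For scale, SHAPE itself is about 6 calls. The column w = 0.5 represents equal arms with every delayed participant measured from the post-wait point.

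**The case against.** **The reach of the restriction is partly inferred.** The Waitlist condition section limits its request to the waiting period and explains it by the comparison between conditions, which ends at 8 weeks. This has some force for that section. Section {15d}, however, is addressed to all participants and refers to the trial as a whole, and sections {27a and 27b} and {34} place the trial's end after the 6-month follow-up.

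**The article does not say that the pre-post CSRI change is itself the saving.** It says that results will be expressed as costs per group. That is correct, but the only comparison it specifies for resource use is the within-group one, and use of healthcare services is named among the savings. Nothing in the text separates restricted services from the rest.

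**Costing categories belong in a health economic analysis plan.** The omission of detail is not the point. The point is that the comparison and its use as savings, as stated, conflict with rules stated in the same article.

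**Stronger readings that the documents do not support.** A reader might infer that a fall in total service use is built in. It is not: only therapy is pushed downward, other care is unrestricted, the rule is an instruction with documented exceptions, and a fall needs participants who had therapy in the before window. That share is not given. Table 1 also excludes people who prefer counselling or trauma-focused therapy within NHS Talking Therapies. Nor does the medication rule create a fall.

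A reader might also infer that a spurious significant result is nearly certain. With 78 people, six sessions each and no use at all afterwards, a paired t-test is significant once 4 or more people had baseline therapy. The probability is about 7% at 2% baseline use, 55% at 5% and 96% at 10%. But if half of the use persists (10% before, 5% after, independently), a significant fall appears in about 19% of simulated trials. The 78 is the primary-outcome requirement, not the number who will receive SHAPE and reach 6 months, and no such test is planned. These percentages describe the assumptions, not the trial.

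**Conclusion.** The point holds in a limited form. As written, the plan can count as a saving a fall in psychological-therapy use that the trial's own rules partly produced, and the Discussion's general caveat does not cover this. The direction for therapy follows from the rules, provided the CSRI as edited for this trial records therapy contacts and looks back over a period that includes time before entry. The size is not determined: the documents give neither the share with therapy in that window, nor the recall window, nor the CSRI items, and the artefact may be zero. For psychotropic medication the conclusion is only that its change is uninformative. The primary and clinical secondary analyses are unaffected.

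**What to change.** In the health economic analysis:

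1. Report psychological therapy and psychotropic medication on separate lines, labelled as restricted by the protocol, and do not count their pre-post change as saved by SHAPE.
2. Base the service-use saving on the unrestricted CSRI categories.
3. State that the pre-intervention point is the one in the Follow-up analyses section (baseline for the immediate arm, post-wait for the delayed arm), give the CSRI recall window, and show the two arms' before periods separately.
4. Optionally, add a between-arm comparison of unrestricted resource use at 8 weeks, from CSRI data already collected. Both arms are then under the same instruction. This comparison cannot show a saving in therapy that both arms were told to avoid, so it does not replace item 1.

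Using the randomisation baseline as the before value for everyone may look tidier but should be avoided. It gives every participant an unrestricted before and a restricted after, and it places the 8-week wait inside the delayed arm's change.

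The cost is some wording and one or two extra table rows. No new data and no change to any trial rule are needed. The downside is that the reported saving may be smaller.
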